### *Setting*

The trial will be conducted in Udon Thani, Thailand. This site was chosen as it was the pilot area for the feasibility pilot of the Thai adaptation of PLH-YC when embedded within the Thai public health system^17. Due to this, the team has positive working relationships between senior and local government officials. Additionally, there are a number of PLH-YC programme facilitators who would be well suited to deliver the ParentChat intervention. These facilitators could be trained in a shortened three-day training course to be ParentChat facilitators. Using the existing pool of PLH facilitators would reduce the cost and time associated with recruitment and training.

### *Sample size*

The estimated sample size was calculated using Stata 17. An exponential test comparing two independent hazard rates was employed based on the primary quantitative outcome, which was the frequency of child maltreatment in the previous month. Given type I error ( $\alpha$ ) < 0.05, power 0.8, allocation ratio 1:1, and applies the effect size in the Hazard ratio using the incidence rate ratio from the recent study of the ParentChat in six countries that showed IRR = 0.57. The result shows that the minimum sample size was 108 (n = 54 in each group). When this is adjusted with an attrition rate of 10%, the minimum sample size is 120 (n = 60 in each group). However, this study uses a cluster random sampling plan, where clusters are sub-district health promotion hospitals (or health centres). To avoid bias and unreliable results, the design effect value must be additionally calculated. It was found that the design effect value is usually between 1 and approximately 5.5,

depending on the difference in size of each cluster. With clusters of similar size, the design effect value will be close to 1. Therefore, it is assumed that the design effect value equals 2 in this study. This means that the sample size will be increased twice and equal to 240.

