To evaluate the hypothesis regarding measuring effectiveness on primary and secondary outcomes, two-tailed tests given a type I error of  $p(\alpha) < 0.05$  and power = 0.8 will be used. Along with the estimated values, 95% confidence intervals and p-values will be presented. Multilevel analysis (MLA) was used to analyse the results because the data is multilevel structured. The data from repeated measurements taken at different times makes up the lowest level. The second level is the individual level, and the third level is the level of sub-district. Primary and secondary outcomes that are on a frequency scale, including child maltreatment, positive parenting, parent exposure to IPV, child/adolescent exposure to risks, online safety, and child learning and development, which are discrete data, will be utilise distribution testes to determine whether to use a Poisson regression or a negative binomial regression if the data is overdispersion. For the ordinal scale outcomes, including parenting stress, attitudes toward corporal punishment, child behaviour problems, parental mental health, and parent support for education, we will use a linear regression to measure the differences between the two groups. A two-level model will be performed comparing post-intervention effects across all outcomes, controlling for baseline and the random effect will be the cluster, and participants ID. In addition, a three-level model will be performed comparing time trends across child maltreatment and proximal outcomes.

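### The sample size and its 80% power come from a two-hazard exponential test, but the primary outcome is a frequency score analysed by Poisson or negative binomial regression, so the stated power is unsupported and could be too high or too low

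*Protocol*

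**What the plan says.** The Sample size section of the Protocol (under C.1) names the method: "An exponential test comparing two independent hazard rates was employed based on the primary quantitative outcome, which was the frequency of child maltreatment". Its inputs are "power 0.8, allocation ratio 1:1", a type I error of 0.05, and an effect size for which the text "applies the effect size in the Hazard ratio using the incidence rate ratio from the recent study of the ParentChat in six countries", a study "that showed IRR = 0.57". Section C.4 specifies "two-tailed tests given a type I error of" 0.05, so the test is two-sided. The outcome of the calculation is: "The result shows that the minimum sample size was 108 (n = 54 in each group". Allowing for 10% attrition gives 120, and an assumed design effect of 2 gives 240.

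The Primary outcome section (C.3) defines the measure as four items, two on physical and two on emotional abuse. Each is a frequency from 0 to 8 or more over the past four weeks, and the items are combined. For outcomes on a frequency scale, C.4 uses distribution tests to "determine whether to use a Poisson regression or a negative binomial regression if the data is overdispersion", within a multilevel model that controls for baseline.

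**The concern.** A hazard-rate test compares times to an event. This trial records how often something happened in a fixed window. A rate ratio and a hazard ratio can share the value 0.57, but the precision with which each is estimated comes from different quantities. For exponential event times it comes from the number of events. For a count it comes from the mean count and any extra-Poisson variation. The Sample size section gives no control mean, event rate, follow-up time, censoring or dispersion.

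At stake is the reading of the primary result. Hypothesis 1 predicts a significant reduction, and C.4 repeats the power of 0.8. If the effect is not significant, readers will take the result as coming from a trial with an 80% chance of detecting a ratio of 0.57, and nothing in the Protocol establishes that.

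**Working it through.** **1. Reproduce the plan's figure.** Inputs from the Protocol: ratio 0.57, two-sided 0.05 (z = 1.96), power 0.80 (z = 0.8416), 1:1 allocation. Set the control hazard to 1; its value cancels. The intervention hazard is then 0.57 and the average 0.785.

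n per arm = [1.96 × √(2 × 0.785²) + 0.8416 × √(1² + 0.57²)]² / (1 − 0.57)²
= (2.176 + 0.969)² / 0.1849 = 53.48, so 54 per arm and 108 in total.

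Then 108 / 0.9 = 120 and 120 × 2 = 240. All three stated figures reproduce.

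**2. What the match implies.** This is the uncensored hazard-difference form, with one observed event per parent. The log-hazard form gives 49.7, so 50 per arm. Censoring at one month gives 98 per arm at a control rate of 1 per month and 68 at 2. It returns to 54 only when the rate is so high (8 per month) that almost nobody is censored. One fully observed event time per parent is therefore an inference from the arithmetic.

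**3. The count-model counterpart.** Let mu0 be the control mean count and k the negative binomial dispersion (variance = mean + k × mean²; k = 0 is Poisson).

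B = 1/mu0 + 1/(0.57 × mu0) + 2k
n per arm = (1.96 + 0.8416)² × B / (ln 0.57)² = 7.849 × B / 0.316 = 24.84 × B
Power = Φ(|ln 0.57| / √(B/54) − 1.96)

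The 54 is the effective number per arm from the plan's own allowances: 240 / 2 × 0.9 = 108, or 54 per arm.

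Example, mu0 = 2 and k = 0.5: B = 0.500 + 0.877 + 1.000 = 2.377; √(2.377/54) = 0.2098; 0.5621/0.2098 − 1.96 = 0.72; power 76%.

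**4. Results.** The Protocol gives neither mu0 nor k, so every value below is an assumption. The total is 2 × (2n/0.9), with 2n/0.9 rounded up.

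| mu0 | k | n per arm | Total after 10% attrition and design effect 2 | Power of the planned 240 |
|---|---|---|---|---|
| 1 | 0 | 69 | 308 | 70% |
| 2 | 0 | 35 | 156 | 94% |
| 2 | 0.5 | 60 | 268 | 76% |
| 2 | 1 | 84 | 374 | 61% |
| 4 | 0.5 | 42 | 188 | 89% |
| 4 | 1 | 67 | 298 | 71% |
| 4 | 2 | 117 | 520 | 48% |

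**5. Break-even.** Power of 80% with 54 per arm needs B of at most 54/24.84 = 2.17. That allows k up to about 0.40 at mu0 = 2 and 0.74 at mu0 = 4. As mu0 grows without limit the first two terms vanish and k may be at most 2.17/2 = 1.09. Above that, this formula reaches 80% at no control mean. At mu0 = 1 it falls short even with k = 0.

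**The case against.** Several points on the other side have force.

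- **A reader might infer that the outcome is overdispersed.** The Protocol does not say so: C.4 makes the negative binomial conditional on a distribution test, and no mean or variance is given anywhere. The point does not need overdispersion, because Poisson power also depends on a control mean that is not stated.
- **A reader might infer that the trial is underpowered.** That is not shown. The variance implied by 54 per arm (B about 2.17) corresponds, at a control mean of 3, to k of about 0.63, a variance of about 8.7. For means of 2 or more it already covers some overdispersion, and several rows of the table exceed 80%.
- **Planned precision gains are left out.** The model controls for baseline and maltreatment is measured four times. If the baseline correlation were 0.5 and cut the variance by about 25%, power at mu0 = 3 would rise from 68% to about 80% with k = 1, and from 46% to about 58% with k = 2. In the other direction, a t reference with 10 degrees of freedom for 12 clusters would lower the 76% at mu0 = 2, k = 0.5 to 68%. The cap of 8 or more per item is ignored throughout.
- **This is a phase II trial of preliminary effectiveness**, and confidence intervals will be reported. That limits the harm. It does not supply a basis for the stated power.

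Nor is this a detail that can be left to an analysis plan: the Protocol itself fixes the test, the effect size, the power and the resulting number.

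**Conclusion.** The point holds as a wrong choice of model. The stated 80% power and the minimum of 108 do not follow from the planned analysis of the primary outcome. It is not an arithmetic slip, since 108, 120 and 240 are all correct for the test named.

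The direction of the error is open. Over the assumed values tabulated, the power of the planned 240 runs from 48% to 94%. These figures take the plan's design effect of 2 and 10% attrition as given, use a normal reference and include no gain from baseline adjustment. The firmest result is conditional: on this formula, dispersion above about 1.09 rules out 80% power at any control mean.

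The paragraph should be corrected, but the point does not undermine the design or the analysis model.

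**What to change.** Replace the hazard-rate calculation in the Sample size section with a Poisson/negative binomial rate-ratio calculation for a cluster trial with 6 clusters of 20 per arm. Take the control mean and dispersion from the pooled baseline data, which can be used without allocation because the Allocation section places randomisation after the baseline assessment. Earlier Thai data would also serve if they used comparable items, which cannot be checked from the Protocol. State both values.

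Keep 240 participants. Report the power at a rate ratio of 0.57, and the rate ratio detectable with 80% power, over a stated range of mean and dispersion. Say whether any gain from baseline adjustment is assumed, and how large.

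The cost is a recalculation and a rewritten paragraph. Enrolment and the analysis model do not change. The stated power may become less favourable.

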### *Programme delivery*

The 120 parents/primary caregivers in the intervention group will be divided into six groups of 20 participants who live in the same sub-districts. Each group will be overseen by one facilitator who will deliver the programme over nine weekly sessions. The group of six facilitators will receive weekly supervision from a trained coach during programme delivery.

Content for the adapted ParentChat programme include six core contents as following: 1) spending quality time with children; 2) talking with children to understand their feelings; 3) using praise and rewards to encourage positive behaviour; 4) establishing limits through effective instruction giving and consistent household rules; 5) nonviolent discipline strategies; and 6) problem solving with children.

Core activities during sessions will be delivered through LINE, a freeware application for instant communication. The programme will provide parents with activity assignments to complete with their children, including text/audio messages, illustrated comics, and videos. The facilitators will moderate text-based discussions around the parenting theme, support parents on an individual basis, and encourage them to apply the parenting skills at home. Parents will be prompted to give feedback regarding successes and challenges applying these parenting skills via audio or text messages during the week. When the next session begins, the facilitators will give a brief voice summary of the feedback and address possible solutions to a few key challenges. During implementation, participants will be supported with the necessary technical support, including IT support. Data bundles will be provided for internet access and to incentivise engagement.

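### The assumed design effect of 2 does not follow from the cluster-size reason given for it, and, separately, the stated power of 0.8 makes no allowance for only 12 randomised clusters

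*Protocol*

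**What the plan says.** Protocol C.1, Sample size, starts from an individual-level calculation: "An exponential test comparing two independent hazard rates was employed". It uses an effect from an earlier multi-country study "that showed IRR = 0.57", together with "power 0.8, allocation ratio 1:1". This gives 108 participants (54 per arm), and 120 after allowing for 10% attrition.

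The section then turns to clustering. It gives a usual range of 1 to about 5.5 for the design effect, "depending on the difference in size of each cluster. With clusters of similar size, the design effect value will be close to 1". The next sentence draws a conclusion from this: "it is assumed that the design effect value equals 2 in this study". The 120 is doubled to 240. No intracluster correlation is given, and the number of clusters does not enter the calculation.

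Other sections fix the design. Twelve sub-districts are randomised 1:1 (Allocation). Each contributes 20 caregivers (Eligibility criteria, Recruitment), and the intervention arm is "divided into six groups of 20 participants who live in the same sub-districts". Section C.4 specifies "two-tailed tests given a type I error of" 0.05, a multilevel model with sub-district as the top level, and post-intervention models that control for baseline. It names no reference distribution or degrees-of-freedom method.

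**The concern.** The stated reason belongs to survey sampling, where unequal cluster sizes and weights inflate variance. In a trial that randomises whole clusters, the inflation comes from the similarity of participants within a cluster, and it is present when every cluster has the same size. The conclusion also does not follow from its premise: sizes are fixed at 20, so the protocol's own rule would give a value near 1, yet it adopts 2. Half of the final sample rests on that factor, and the parameter that determines it is not stated.

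The second matter is independent of the first. Multiplying by a design effect corrects the variance but still assumes a large-sample test. Six clusters against six leave about 10 degrees of freedom for the between-cluster comparison. If this is ignored, either the power or the type I error is not what the protocol states. A null result would then be read against a power that the design may not have.

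**Working it through.** **1. Reproducing the protocol's figures.** Inputs from Sample size: ratio 0.57, alpha 0.05, power 0.8, 10% attrition, design effect 2. Two-sided testing comes from C.4. For the exponential test on the hazard difference without censoring:

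n per arm = [1.960 x √2 x (1 + 0.57)/2 + 0.842 x √(1 + 0.57²)]² / (1 - 0.57)² = (2.176 + 0.969)² / 0.1849 = 53.48, rounded up to 54.

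Total 108; 108/0.9 = 120; 120 x 2 = 240. All three match, so the arithmetic is correct.

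**2. The ICC implied by 2.** With equal clusters, design effect = 1 + (m - 1) x ICC.
- m = 20 (as recruited): ICC = 1/19 = 0.053.
- m = 18 (20 x 0.9): ICC = 1/17 = 0.059.

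At ICC = 0.053 with 18 analysed, the design effect is 1 + 17/19 = 1.89.

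**3. Power with 6 clusters per arm.** Analysed per arm: 6 x 18 = 108. Effective n per arm: 108/2 = 54, or 108/1.89 = 57. The t reference has 12 - 2 = 10 df and a two-sided critical value of 2.228. Three ways of setting the signal size were used:
- (a) 54 effective per arm taken as exactly 80% power: non-centrality (1.960 + 0.842) x √(n/54), which is 2.80 at n = 54.
- (b) the protocol's own hazard-difference test, with t in place of the normal.
- (c) the log ratio: √(n/2) x |ln 0.57| = √27 x 0.562 = 2.92 at n = 54.

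| Reading of design effect 2 | Effective n per arm | t, 10 df: (a) / (b) / (c) | Normal: (a) / (b) / (c) |
|---|---|---|---|
| Holds among the 18 analysed | 54 | 0.714 / 0.722 / 0.749 | 0.800 / 0.804 / 0.832 |
| Holds at 20, 18 analysed (1.89) | 57 | 0.737 / 0.744 / 0.772 | 0.821 / 0.824 / 0.851 |

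**4. Cost of keeping the normal reference.** If the statistic follows t on 10 df and is compared with 1.96, the two-sided type I error is 2 x P(T > 1.96) = 0.078, not 0.05.

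**5. Sensitivity to the ICC.** The ICC values are assumptions, since the protocol gives none. With 18 analysed per cluster and t on 10 df:

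| ICC | Design effect, 1 + 17 x ICC | Power, (a) to (c) |
|---|---|---|
| 0.02 | 1.34 | 0.87-0.89 |
| 0.05 | 1.85 | 0.75-0.78 |
| 0.10 | 2.70 | 0.59-0.62 |

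Solving for power 0.80 gives an ICC of 0.037 under (a) and 0.045 under (c).

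**The case against.** Four arguments can be made for the protocol.

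- **The value 2 is labelled an assumption and is more cautious than the reason given for it.** This is true: the protocol doubled its sample where its own rule would have given a value near 1. It makes 2 a possibly reasonable guess, but it does not supply the missing ICC.
- **The protocol names no degrees-of-freedom method, and a statistical analysis plan may do so.** This stands, and it makes the lower power conditional on a t reference. It does not rescue the power statement, because with the normal reference the type I error moves instead. Before any other adjustment, alpha 0.05 and power 0.8 do not hold together on the protocol's own inputs.
- **Baseline adjustment is planned and ignored here.** This also stands. The protocol gives no correlation, so the gain can only be illustrated. If baseline removed 10% of the outcome variance at both levels, power under (a) at design effect 2 would be about 0.76; 20% would give about 0.81. Overdispersion of the counts could act the other way and is equally unquantified.
- **The trial is phase II and seeks preliminary effectiveness.** This lowers the stakes. However, B.4 states hypotheses of significant effects and the protocol states a power, so that power should be supportable.

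A reader might infer that the mistaken rationale itself causes the loss of power. It does not: if 2 is the right value, the rationale costs nothing, and the drop comes wholly from the small number of clusters. A reader might also infer that the trial's power is simply 0.71-0.75, or that 240 is miscalculated. The documents support neither. The first depends on an unnamed reference distribution and omits the planned baseline adjustment; the second is refuted by the exact reproduction of 108, 120 and 240.

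**Conclusion.** Both defects hold, and each stands without the other. The reason given for the design effect is wrong for a cluster-randomised comparison of equal clusters. The value 2 is therefore unsupported in either direction and conceals an ICC of 0.053-0.059. The power of 0.8 also carries no allowance for 12 clusters. With t on 10 df it is about 0.71-0.75 if the design effect is 2 among those analysed, or 0.74-0.77 if 2 applies at recruitment. With a normal reference at design effect 2 it stays at about 0.80-0.83, at a true two-sided alpha of about 0.078 if the statistic follows t on 10 df.

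These figures take the 54 effective participants per arm as given, without judging whether a hazard-rate test suits a frequency outcome. They also assume equal clusters and 10% attrition spread evenly, and they precede baseline adjustment and overdispersion. This is an unsupported assumption and an incomplete power statement, not an arithmetic error.

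**What to change.** In C.1, Sample size:

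1. Delete the statement that similar-sized clusters bring the design effect close to 1.
2. State design effect = 1 + (m - 1) x ICC, with m = 20 (18 after attrition), and say that 2 corresponds to an ICC of 0.053 or 0.059 respectively.
3. Name a small-sample reference for the between-cluster comparison (about 10 df), and make the analysis consistent with it.
4. Replace the flat 0.8 with power over an assumed ICC range, such as the table under step 5 of the working. Say that 0.80 before baseline adjustment needs an ICC of about 0.037-0.045 or less. Any gain claimed from baseline adjustment should come with its assumed correlation.

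The 240 participants and 12 clusters can stay. The cost is some protocol wording, a short table, and a less favourable stated power.

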### *Recruitment*

This study will use a two-stage cluster sampling to recruit 240 parents or caregivers. Groups will start to operate after 20 members per group are recruited. The general recruitment strategy is described as follows:

Clusters are 12 sub-districts in Udon Thani, which will be randomly selected for the study. Some of the sub-districts that had been included in the previous study will be excluded at the stage of clusters sampling to prevent contamination bias. If there is more than one health promotion hospital in some sub-districts, only one will be selected at random. Twelve health-promoting hospitals in the selected sub-districts will be invited to partner with researchers to:

1. Provide researchers with a list of 20 randomly selected children aged 2 to 17 from each Health Promoting Hospital's database.
2. Coordinate contact with the selected children's parents/caregivers.

However, suppose the health-promoting hospitals do not allow or cannot use the randomly selected method. In that case, they can consider referring parents who could benefit from a programme that helps them manage difficult child behaviours.

Data collectors will conduct a screening interview with parents/caregivers to determine whether they meet the eligibility requirements of the study.

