##### *Eligibility criteria*

The following are the inclusion and exclusion criteria for participating parents or caregivers ( $n = 20$  per cluster):

Inclusion criteria for parents or caregivers:

1. Primary caregiver over the age of 18 years currently caring for child between the ages of 2 to 17;
2. Has regular contact with the child and lives with the child for at least 4 nights per week;
3. Has access to a smartphone and is willing and available to join an online parenting support group to share, learn and discuss parenting; and
4. Has provided consent to participate in the study.

Exclusion criteria for parents or caregivers

1. Exhibiting severe mental health problems or acute mental disabilities
2. Already participated in the PLH-YC Thailand programme or other parenting programmes. Other parenting programmes would not include Parent Schools in Mother and Child Health clinics at public hospitals, which are provided in all provinces and districts in Thailand as 'standard care'.

The study will also assess the process of implementation.

Inclusion criteria for programme facilitators, who will deliver ParentChat, consist of the following:

1. Age 18 or older;
2. Prior completion of a ParentChat facilitator training workshop;
3. Agreement to implement the entire programme; and
4. Provision of consent to participate in the full study.

Inclusion criteria for in-depth interviews with caregivers (n = 12):

1. 4 high engagement (participate  $\geq$  6 sessions)
2. 4 low engagement (participate  $\leq$  4 sessions)
3. 4 participants who drop out before 4th session
4. Provides consent to participate in the interview

Inclusion criteria for focus groups with facilitators:

1. Age 18 or older;
2. Have delivered the entire ParentChat programme; and
3. Provision of consent to participate in the full study.

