### *Allocation*

The 12 sub-districts will be randomly assigned using a 1:1 allocation ratio to either the intervention or control group using a computer programme after baseline assessment, and the groups will be set up. The random sequence will be produced by an outside researcher working at the HIV Netherlands Australia Thailand Research Collaboration (HIV-NAT) who is not directly participating in the project. Following the gathering of baseline data, the project coordinator and co-investigator will contact participants via telephone to inform them of their allocation status, ensuring that participants are blinded to their status throughout the initial evaluation.

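### The random lists hold exactly as many names as there are places, with no replacement rule, and a per-hospital referral route may differ between clusters with no stated balancing at allocation

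*Protocol*

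**What the plan says.** All of this is in the protocol, mainly section C.1.

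- **Target and clusters (Recruitment).** "This study will use a two-stage cluster sampling to recruit 240 parents or caregivers". "Clusters are 12 sub-districts in Udon Thani, which will be randomly selected for the study". With 12 clusters this is 20 participants per cluster, the figure that Eligibility criteria also gives.
- **List.** Each partner hospital is asked to "Provide researchers with a list of 20 randomly selected children aged 2 to 17 from each Health Promoting" Hospital's database.
- **Start rule.** "Groups will start to operate after 20 members per group are recruited".
- **Screening.** "Data collectors will conduct a screening interview with parents/caregivers to determine whether they meet the eligibility requirements of the study". The criteria include smartphone access, living with the child at least 4 nights a week, no earlier parenting programme and no severe mental health problem. Consent is voluntary (section D.1).
- **Fallback.** Where a hospital refuses or is unable to sample at random, "they can consider referring parents who could benefit from a programme that helps them manage difficult child behaviours".
- **Allocation.** The unit is the sub-district, and all of them "will be randomly assigned using a 1:1 allocation ratio to either the intervention or control group using a computer programme after baseline assessment", with the sequence produced by an outside researcher. No stratification, matching or other restriction is named.
- **Analysis (section C.4).** The post-intervention model adjusts for the baseline value and has a random effect for cluster. It names no term for recruitment route.

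**The concern.** There are two separate weaknesses.

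First, the number of names equals the number of places, although losses at contact, screening and consent are built into the procedure. The 10% inflation under Sample size is for attrition and does not cover these losses. The text does not tell field staff what to do when a sampled family is lost. If each site improvises its own replacements, the second stage of the two-stage sample is no longer a random sample.

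Second, the fallback admits a differently selected population, chosen for difficulty with child behaviour, and it operates hospital by hospital. Hospitals correspond one-to-one with the randomised clusters, so a mixture of routes is a difference between clusters. Child behaviour problems are a secondary outcome, and harsh discipline, the primary outcome, may plausibly be related to route. With 6 clusters per arm, simple randomisation is a weak guard against such a difference. Because baseline is complete before allocation, the information needed to balance it is already in hand.

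**Working it through.** **1. The plan's own sample size.** Inputs from Sample size (C.1): rate ratio 0.57 used as a hazard ratio, power 0.8, 1:1 allocation, alpha 0.05. C.4 makes the test two-sided. For a two-sample exponential test on the hazard difference with λ1 = 1, λ2 = 0.57 and mean 0.785:

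N = [1.960 × √(4 × 0.785²) + 0.842 × √(2 × 1² + 2 × 0.57²)]² / 0.43² = 106.96, which is 108 when rounded to 54 per arm.

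108 / 0.90 = 120, and 120 × 2 (design effect) = 240. The stated 108, 120 and 240 all reproduce. The arithmetic is not at fault here.

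**2. Names against places.** 12 hospitals × 20 names = 240 names, and 12 groups × 20 places = 240 places. The slack is zero.

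**3. What losses do.** Let y be the proportion of listed families that are reached, eligible and consenting. The protocol gives no value, so the range below is an assumption, and families are treated as independent. P(one list fills 20 places) = y^20, expected enrolment from the lists = 240y, and names needed per hospital on average = 20/y, rounded up.

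| Yield y | Expected enrolment | P(one group filled) | Names needed per hospital (total) |
|---|---|---|---|
| 100% | 240 | 1 | 20 (240) |
| 95% | 228 | 0.36 | 22 (264) |
| 90% | 216 | 0.12 | 23 (276) |
| 80% | 192 | 0.012 | 25 (300) |
| 70% | 168 | 0.0008 | 29 (348) |
| 50% | 120 | below 0.0001 | 40 (480) |

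At 95%, the probability that all 12 groups fill is 0.95^240 = 4.5 × 10⁻⁶.

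**4. Chance imbalance in route.** There are C(12,6) = 924 ways to split 12 clusters 6:6. The number of referral clusters is not known in advance, so these counts are illustrations.

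- 2 referral clusters: both in one arm in 2 × C(10,4) = 420 splits, and 420/924 = 0.455.
- 4 referral clusters: a 3:1 split in 2 × C(4,3) × C(8,3) = 448 splits (0.485) and a 4:0 split in 2 × C(8,2) = 56 splits (0.061). Together 504/924 = 0.545.
- 6 referral clusters: 4:2 or worse in 2 × (225 + 36 + 1) = 524 splits, and 524/924 = 0.567.
- 0 or 12 referral clusters: route does not vary, so there is nothing to balance.

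**5. Room for restriction.** With 4 referral clusters, 924 − 504 = 420 allocations split them 2:2. That leaves a large set from which to choose at random while also balancing the cluster mean baseline abuse score.

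**The case against.** - **The target is not impossible.** A reader might infer that 240 cannot be reached by random sampling. The protocol presents its text as a general strategy and does not forbid a second random draw. What is missing is a rule for replacements. This stands.
- **A loss of power is not shown.** A reader might take 80% yield, giving 192 enrolled and about 173 after 10% attrition, and read off a fall in power from 0.80 to about 0.71 with the design effect held at 2. That requires an assumed yield and groups starting below 20, which the start rule excludes if followed. Delay or undocumented top-up is at least as likely.
- **The fallback is not a response to shortfall.** Its stated trigger is a hospital's refusal or inability to sample at random. Clusters differ in route only if some hospitals, but not all, use it.
- **Size of the difference.** No figure in the protocol shows that referred families have higher baseline abuse, or that mixing routes would push between-cluster variance past the assumed design effect of 2. Both are plausible; neither is established.
- **Mitigation exists.** Section C.4 adjusts for baseline, which removes part of any difference carried by the baseline score. Route is settled before allocation and so cannot depend on arm. A reader might call this selection bias between arms, but the order of events rules that out.
- **Silence on restriction.** The Allocation text does not say that stratification is absent, and a separate randomisation document might specify it. That is fair, but as written only the ratio is fixed.

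These points narrow the concern. They do not supply a replacement rule or a way of handling mixed routes.

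**Conclusion.** The point holds in a limited form. As written, the random lists deliver 240 participants only at a 100% yield. Even at an assumed 95%, a given hospital is more likely than not to fall short (1 − 0.36 = 0.64), and at least one of the 12 almost certainly will. The consequence is waiting, short groups or unplanned top-up; how much power, if any, is lost cannot be derived from the protocol.

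On route, the exposure is conditional on a mixture across hospitals. Where there is one, a 6:6 allocation with no restriction leaves a difference of at least two referral clusters between arms with probability 0.455, 0.545 or 0.567 for 2, 4 or 6 referral clusters. Most of the 0.545 is 3:1 (0.485); 4:0 is 0.061. This is chance imbalance and added between-cluster variance, partly absorbed by baseline adjustment, and does not make the comparison systematically biased. The changes are worth making because they are cheap and use information that will exist before allocation.

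**What to change.** **Recruitment (C.1).** Ask each hospital for a longer list in random order, for example 40 names, and approach families strictly in that order until 20 are enrolled. Forty names match an average yield of 50%; a further random draw should be allowed if a list runs out. Record for each cluster whether families came from random selection or referral.

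**Allocation (C.1).** Since baseline precedes allocation, have the outside researcher stratify or constrain the 6:6 allocation on recruitment route (if routes are mixed) and on cluster mean baseline abuse score, choosing at random among the acceptable splits.

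**Analysis (C.4).** Account for route in the model if it varies.

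**Cost.** A longer database extract and a short allocation program; no extra visits, participants or instruments. Adding route as a cluster-level covariate uses about one of roughly 10 between-cluster degrees of freedom (12 clusters − 2 arms), which is a real price in a trial of this size.
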